**Methods/design:**

In a multicenter, randomized controlled trial we are evaluating the efficacy of two intensities of light therapy in reducing CRF complaints and restrictions caused by CRF in survivors of Hodgkin lymphoma or diffuse large B-cell lymphoma. Secondary outcomes include sleep quality, depression, anxiety, quality of life, cognitive complaints, cancer worries, fatigue catastrophizing, self-efficacy to handle fatigue, biological circadian rhythms of melatonin, cortisol and activity, and biomarkers of inflammation. We will recruit 128 survivors, with fatigue complaints, from academic and general hospitals. Survivors are randomized to either an intervention (exposure to bright white light) or a comparison group (exposure to dim white light). The longitudinal design includes four measurement points at baseline (T0), post-intervention at 3.5 weeks (T1), 3 months post-intervention (T2) and 9 months post-intervention (T3). Each measurement point includes self-reported questionnaires and actigraphy (10 days). T0 and T1 measurements also include collection of blood and saliva samples.

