### Study procedure

All participants complete a battery of self-report questionnaires and wear a wrist actigraph at four different measurement points (T0: baseline; T1: directly after 3,5 weeks of light therapy; T2: 3 months after light therapy; T3: 9 months after light therapy). The first (T0) and second (T1) measurement points include a visit to the hospital to provide participants with materials and instructions, to perform cognitive tests, and to collect blood (during the visit) and saliva (on day 8 and 36) samples. Figure 2 shows a schematic diagram of a participant’s timeline.

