#### Outcome measures

The Multidimensional Fatigue Inventory (MFI) [41], a VAS-scale for fatigue [42] and the Work and Social Adjustment Scale (WSAS) [43] are the primary outcome measure of this study. Secondary outcome measures include: Pittsburg Sleep Quality Index (PSQI) [44], wrist actigraphy [45], Center for Epidemiological Studies – Depression scale (CES-D) [46], State-Trait Anxiety Inventory-6 items (STAI-6) [47], Medical outcome studies short form (SF-36) [48], Medical Outcomes Studies Cognitive function scale (MOS-CF6) [49], MD Anderson Symptom Inventory (MDASI) [50], Psychomotor Vigilance Task (PVT) [51], 15 words task [52], digit span task [53], cancer worry scale (CWS) [54], fatigue catastrophizing scale (FCS) [55], Self-efficacy scale 28 (SES-28) [56], salivary cortisol and melatonin, and inflammatory biomarkers. Detailed descriptions of these outcome measures are provided in Table 1.

**Table 1 Tab1:** Study outcome measures and corresponding questionnaires

Variable	Questionnaire	Number/type of items	Time frame	Score range	Psychometric details
Primary outcomes					
Cancer related fatigue	MFI [41]	20 four-point Likert scale	Past few days	Subscale scores: 4–20; higher scores indicate more fatigue	Subscales: general fatigue, mental fatigue, physical fatigue, reduced motivation, reduced activity. Cronbach’s alpha: 0.84
	VAS-scale [42]	1 eleven-point Likert scale	This moment	0–10; higher scores indicate more fatigue	
Restrictions caused by fatigue	WSAS [43, 70]	5 nine-point Likert scale	Influence of fatigue on daily life	0–40; higher scores indicate higher levels of disability	Cronbach’s alpha: > 0 .79
Secondary outcomes					
Sleep quality	PSQI [44]	19 four-point Likert scale and open-ended questions	Past month	Total score: 0–21 Subscale scores: 0–3; higher scores indicate more acute sleep disturbances	Subscales: subjective sleep quality, sleep latency, sleep duration, habitual sleep efficiency, sleep disturbances, use of sleeping medication, daytime dysfunction. Cronbach’s alpha: 0.83
Depression	CES-D [46, 71]	20 four-point Likert scale	Past week	0–60; higher scores indicate greater depressive symptoms	Cronbach’s alpha: 0.85–0.90
Anxiety	STAI-6 [47]	6 four-point Likert scale	This moment	20–80; higher scores indicate increased anxiety	Cronbach’s alpha: 0.83

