##### Blood samples

Blood samples are collected to measure biomarkers of inflammation and vitamin D at baseline. During T0 and T1, two tubes of 10 mL of blood will be collected. One of these tubes will be saved in the biobank NKI-AVL. The other will be used to assess vitamin D and the following inflammatory biomarkers in duplicate by ELISA: IL-1RA, hsIL-6, sTNF-RII, and hsCRP. Vitamin D has been associated with current levels of fatigue [60–62]. The before-mentioned biomarkers have previously been associated with fatigue in patients with cancer [35, 63]. The level of these biomarkers, as well as the change in biomarker levels will be used as parameters for the statistical analysis.

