#### Statistical analyses

Data will be analysed using the Statistical Package for the Social Sciences (SPSS). Although we endeavour to check all questionnaires upon their return and call participants to complete missing items, some data might still be missing. Missing values will be imputed according to the manual of the questionnaire. In general, descriptive statistics will be computed for the outcome variables, potential covariates and demographic variables. Bivariate analyses will be undertaken to explore associations between outcome and potentially confounding variables (e.g. season, diagnosis, years since diagnosis) using correlations (for continuous variables) and Chi-square tests (for categorical variables).

Group differences in change in fatigue during the trial will be investigated using a mixed effect growth model with random intercept and slope, nested within site (clusters of different hospitals). This approach takes into account the within and between person variability, and deals adequately with missing data [66]. If baseline differences are identified despite randomisation, these variables will be accounted for in the model. In case of non-ignorable dropout we will correct the model for different patterns of missing values [67]. All analyses will be done on an ´intention to treat´ basis. Additional explorative analyses will be done on a ´per protocol´ basis.

The mixed effect model approach described for change in fatigue will also be used to determine treatment effects of continuous secondary outcome measures. To evaluate between-group differences in categorical secondary outcome measures, we will use generalized estimating equations (GEE) for longitudinal data. This approach accounts for correlated within subject responses, allows for not normally distributed variables and deals adequately with missing data [67–69]. Since there are multiple outcomes, the *p*-values for each model will be adjusted for multiple comparisons.

Within the intervention group we will explore which variables are predictive for the efficacy of light therapy in reducing fatigue. A mixed effect model for longitudinal data will be used with fatigue as dependent variable and the following independent variables: sleep quality, depression, anxiety, cognitive complaints, quality of life, and biological circadian rhythms. The *p*-values will be adjusted for multiple testing.

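### The random-intercept-and-slope growth model is extended to secondary outcomes measured only at T0 and T1, where its variance components cannot be separated

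*Protocol article*

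**What the plan says.** For fatigue, the protocol article (Statistical analyses) specifies a "mixed effect growth model with random intercept and slope, nested within site (clusters of different hospitals". It does not state the covariance structure of the random effects. The same section then extends the approach: "The mixed effect model approach described for change in fatigue will also be used to determine treatment effects of continuous secondary outcome measures".

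The Outcome measures section lists among the secondary outcomes the Psychomotor Vigilance Task, the 15 words task and the digit span task, together with "salivary cortisol and melatonin, and inflammatory biomarkers".

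The measurement schedule differs by type of outcome:

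- Questionnaires and actigraphy have four occasions: "Each measurement point includes self-reported questionnaires and actigraphy (10 days" (Abstract, Methods/design).
- Blood and saliva have two: "T0 and T1 measurements also include collection of blood and saliva samples" (same place).
- Cognitive tests have two. Study procedure ties them to the hospital visits at T0 and T1, which serve among other things "to perform cognitive tests, and to collect blood (during the visit) and saliva (on day 8 and 36) samples".

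On the blood markers, the Blood samples section adds: "The level of these biomarkers, as well as the change in biomarker levels will be used as parameters for the statistical analysis". It does not say whether the level or the change carries the treatment comparison.

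**The concern.** A random slope describes how each person's trajectory departs from the group trajectory. With two measurements per person, that departure cannot be told apart from residual error unless a further restriction is imposed. The article states no such restriction, yet it names this model as the treatment-effect analysis for the hormone and inflammation parts of secondary objective 2 and for the objective cognitive tests.

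If the model is run as written, the software may fail to converge, report variance components that are one arbitrary choice among many, or give no standard errors for them. Degrees-of-freedom methods that use the precision of the variance components, such as Satterthwaite's, then have no sound basis. Someone would have to choose a replacement model outcome by outcome after seeing the data. Having both level and change as biomarker parameters adds to that freedom.

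**Working it through.** **Background check.** The article's sample size reproduces. For d = 0.5, two-sided alpha 0.05 and 80% power, the normal approximation gives 63 per arm, and 64 per arm under the t test has power 0.801. The point below does not depend on this.

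**Parameter count.** For one person measured at times t_j and t_k, the model implies

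Cov(Y_j, Y_k) = σ²_int + (t_j + t_k)·σ_int,slope + t_j·t_k·σ²_slope + σ²_res·1(j = k).

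That is four parameters. With m occasions there are m(m + 1)/2 distinct variances and covariances.

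| Occasions | Distinct (co)variances | Parameters | Rank | Identified? |
|---|---|---|---|---|
| 2 (T0, T1) | 2·3/2 = 3 | 4 | 3 | No |
| 4 (T0 to T3, about 0, 3.5, 16.5 and 42.5 weeks) | 4·5/2 = 10 | 4 | 4 | Yes |
| 2, random intercept only | 3 | 2 | 2 | Yes |

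The article's site term does not help, because it does not separate the person-level components. Nor do the repeated saliva samples within a day. They are reduced to the awakening response, diurnal slope, area under the curve and DLMO, so each summary has one value per occasion.

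**What this does to a fit.** In simulated two-visit data (64 per arm, assumed covariances), the sample variances were 0.858 at T0 and 0.741 at T1, with covariance 0.437. Two very different parameter sets reproduce them:

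- Residual 0.05, intercept variance 0.808, covariance −0.371, slope variance 0.625. Then T0: 0.808 + 0.05 = 0.858; covariance: 0.808 − 0.371 = 0.437; T1: 0.808 − 2(0.371) + 0.625 + 0.05 = 0.741.
- Residual 0.30, intercept variance 0.558, covariance −0.121, slope variance 0.125. Then T0: 0.558 + 0.30 = 0.858; covariance: 0.558 − 0.121 = 0.437; T1: 0.558 − 2(0.121) + 0.125 + 0.30 = 0.741.

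Residual variances of 0.05, 0.10, 0.20 and 0.30 all gave the same REML log-likelihood, −74.966.

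**What stays estimable.** In a second simulated data set with complete visits, the group-by-time estimate was −0.756 with SE 0.156, both with and without the random slope. Standard errors for the variance components were not returned when the slope was included.

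**Uncorrelated random effects.** Setting the intercept–slope covariance to zero leaves three parameters. With time coded 0/1 the rank is 3, so the model is just identified. With centred time the rank is 2, and it is not. Under 0/1 coding the slope variance equals Var(T1) − Var(T0). With equal true variances its estimate was negative, hence on the boundary, in about 51% of simulations.

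**Gain from baseline adjustment.** With complete two-visit data and freely estimated arm means at both visits, the arm-by-time contrast is the difference in mean change. Assume equal variances at T0 and T1 and correlation r (not given in the article):

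- Variance of change: 2(1 − r)σ².
- Residual variance after adjusting T1 for T0: (1 − r²)σ².
- Ratio: (1 − r²)/[2(1 − r)] = (1 + r)/2.

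At r = 0.3, 0.5 and 0.7 the ratio is 0.65, 0.75 and 0.85, which is 35%, 25% and 15% less variance.

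For DLMO (25 per condition, two-sided 0.05, 80% power, t test) the detectable effect is 0.809 SD of the change score. At r = 0.5 it becomes 0.809 × √0.75 = 0.70. At that r, the change SD is √(2 × 0.5) = 1 times the single-visit SD, so the two scales coincide. This ignores the few degrees of freedom spent on covariates.

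**The case against.** The strongest reply is that the treatment comparison survives. Only the variance components are unidentified, and with complete data, dropping the slope changed neither the estimate nor its standard error. That stands. A reader might infer that the biological treatment effects cannot be estimated at all, or that their p-values hang on a software default; the check above does not support this.

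Second, the article gives no random-effects covariance structure, so the fourth parameter comes from the usual default. This is correct, but the uncorrelated alternative is only just identified, depends on how time is coded, and often lands on the boundary.

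Third, a journal article is condensed, and a full analysis plan may give a structure for each outcome. The sentence on biomarker change also suggests that something other than a growth curve may have been intended. This lowers the weight of the point. Still, the article makes a positive statement covering every continuous secondary outcome, and any workable plan for the two-visit outcomes has to depart from it.

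Fourth, the efficiency figures measure the benefit of baseline adjustment, not the identifiability defect. Agreed; they support the choice of replacement only.

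A reader might also suppose that skewed concentrations are to be analysed untransformed. The article says nothing on scale and reports no distributions, so no such criticism is made.

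**Conclusion.** The point holds in limited form. For the cortisol summaries, DLMO, inflammatory markers and cognitive tests, the stated model with correlated random effects asks for four variance parameters from three observable moments. The consequence is non-convergence, arbitrary variance components and an unplanned choice of model per outcome, not loss of the treatment comparison.

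It would be wrong to extend this to the whole of secondary objective 2 or to every mechanism analysis. Objective 2 also covers activity rhythms, recorded at all four measurement points. Objective 3 has its own within-arm model with fatigue, measured four times, as the dependent variable. The primary outcomes and the other questionnaires are unaffected.

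The count follows from the article alone, given the usual correlated structure. The 15% to 35% gain and the DLMO figures rest on assumed r and equal variances at the two visits. This is a specification error in secondary analyses that should be corrected.

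**What to change.** Add one sentence to the analysis plan for outcomes measured only at T0 and T1. Either of these would do:

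- Regress the T1 value on arm, the T0 value and the minimisation factors (diagnosis, time since diagnosis, gender).
- Fit a two-visit repeated-measures model with unstructured covariance, a common baseline mean for the two arms and no random slope.

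Name one as the analysis for these outcomes. For the blood markers, state that this baseline-adjusted comparison at T1 is the treatment effect, so that level and change are not competing analyses. Keep the growth model for outcomes with four occasions.

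The cost is wording only: no new data, no change in sample size and no effect on the primary analysis.

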A third potential mechanism is the normalizing effect of light therapy on the HPA axis, which may affect inflammatory cytokine activity. There is a wealth of research, both in animals as well as in clinical and healthy human populations, showing strong interconnections between fatigue and inflammation. Consistent associations have been shown between CRF and plasma levels of inflammatory markers such as interleukin-6 and C-reactive protein [35, 36]. There is also a well characterized feedback loop between the HPA axis and inflammation, whereby the HPA axis can down regulate inflammation and is itself up regulated by inflammatory signaling [37]. BWL has been found to normalize HPA axis function [38] raising the possibility that BWL may affect inflammatory cytokine activity either directly or indirectly, e.g., via its normalizing effects on the HPA axis.

The main aim of this double-blind, randomized controlled trial, called ‘improving Sleep quality, Psychosocial functioning and cAncer Related fatigue with Light thErapy (SPARKLE)’, is to determine the effect of exposure to BWL compared to exposure to dim white light (DWL), on CRF in ≥2 years survivors of HL and DLBCL. Additionally, this trial will explore potential mechanisms of light therapy on CRF by investigating the influence of light therapy on factors associated with CRF. More specific, the secondary objectives are:to examine the effect of exposure to BWL compared to DWL on sleep quality and psychological variables (depression, anxiety, cognitive complaints, and quality of life).to investigate whether exposure to BWL, compared to DWL, affects circadian rhythms of cortisol and melatonin, activity, vitamin D concentrations and levels of biomarkers for inflammation markers.to explore whether the effects of exposure to BWL on CRF can be predicted by the effect of BWL on sleep quality, psychological variables, biological and activity circadian rhythms, and inflammation markers.

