##### Salivary melatonin

A subgroup (*n* = 25 per condition) will be asked to collect five additional saliva samples in the evening to determine the *Dim Light Melatonin Onset* (DLMO). Starting point for this saliva collection will be 5 h prior to usual bedtime followed by one sample every sequential hour. Previous research indicated that these time points provide a reliable measurement for DLMO with at home collected saliva samples [58]. Participants receive the additional instruction to collect these samples in dim light conditions.

A commercial direct saliva melatonin radioimmunoassay (RIA; Bühlmann laboratories, Schönenbuch, Switzerland) will be used to assess melatonin levels in saliva. The DLMO will be determined based on a threshold of 4.0 pg/mL. Previous research indicated that a fixed threshold is the most convenient way to determine DLMO although there is a risk that DLMO cannot be determined in patients with sleep problems as a consequence of low secretion of melatonin [58]. When we address this problem in the current study, an alternative procedure will be used. DLMO will then be defined as the time when melatonin concentration is two SD above the basal mean of three daytime samples [59].

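### The analysis of what predicts the efficacy of light therapy uses only the bright-light arm, so it cannot answer the third secondary objective, which concerns effects of bright against dim light

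*Protocol article*

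**What the plan says.** Three parts of the Protocol article bear on this.

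- **Objective.** The Background states that "this trial will explore potential mechanisms of light therapy on CRF by investigating the influence of light therapy on factors associated with CRF". The third secondary objective is "to explore whether the effects of exposure to BWL on CRF can be predicted by the effect of BWL on sleep quality", and it goes on to name psychological variables, biological and activity circadian rhythms, and inflammation markers. The main aim, in the same section, defines the effect of BWL by comparison with DWL.
- **Analysis for that objective.** Under Statistical analyses: "Within the intervention group we will explore which variables are predictive for the efficacy of light therapy in reducing fatigue". The model is given: "A mixed effect model for longitudinal data will be used with fatigue as dependent variable and the following independent variables", namely "sleep quality, depression, anxiety, cognitive complaints, quality of life, and biological circadian rhythms". It has no treatment term, since only one arm enters. On multiplicity: "The *p*-values will be adjusted for multiple testing". The method of adjustment is not named.
- **Two-arm analyses.** The groups are compared on change in fatigue, and "The mixed effect model approach described for change in fatigue will also be used to determine treatment effects of continuous secondary outcome measures".

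The article therefore fixes both the population and the form of this analysis. It is not a detail left open for a fuller document.

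**The concern.** Efficacy is a difference between randomized arms, and it cannot be observed inside one of them. In BWL patients alone, a slope of fatigue on sleep quality or depression mixes whatever the light did with whatever would have happened anyway:

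- placebo response;
- regression to the mean, because patients are selected for high fatigue (Participants);
- content shared between self-report scales: in Table 1 the SF-36 has a vitality subscale and the PSQI a daytime dysfunction subscale.

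All of these act under dim light too. The model could therefore name predictors of efficacy among variables that bright light leaves untouched. At stake is the answer to the third secondary objective and any mechanism conclusion drawn from it.

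**Working it through.** **1. The plan's own figure.** The Sample size calculation gives 64 per group, an effect size of 0.5, alpha 0.05 and 80% power. A two-sided two-sample t-test with these inputs has power 80.1%, and it needs 63.8, so 64, per group. The figure reproduces and is not disputed. The article gives no figure for the predictor analysis.

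**2. Objective against analysis.**

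| Quantity the objective needs | Where it can be estimated | Planned? |
|---|---|---|
| Effect of BWL against DWL on fatigue | both arms | yes, primary mixed model |
| Effect of BWL against DWL on each candidate variable | both arms | yes, for continuous secondary outcomes |
| Link between these two effects | both arms | no; the only model relating fatigue to the candidates uses BWL patients |

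**3. How often the one-arm test flags a variable that BWL does not change.** Assumptions, none from the documents: the change in one candidate and the change in fatigue correlate at r, equally in both arms; BWL has no effect on the candidate; all 64 patients are analysed; one variable is tested at a time. This simplifies the planned longitudinal model.

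Fisher-z approximation: probability of a significant result = Φ(artanh(r) × √(64 − 3) − z), with z = 1.960 at alpha 0.05 and z = 2.638 at alpha 0.05/6.

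Example, r = 0.3: artanh(0.3) = 0.3095; 0.3095 × √61 = 2.417. Then Φ(2.417 − 1.960) = 0.68 and Φ(2.417 − 2.638) = 0.41.

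A simulation (4,000 trials per setting, 64 per arm) checks this and adds two two-arm tests: (i) the interaction of arm with the candidate's change, and (ii) joint significance of the arm-to-candidate path and the candidate-to-fatigue path adjusted for arm. The simulated columns are for BWL without effect on fatigue.

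| r | One arm, 0.05 (formula) | One arm, 0.05 (simulated) | One arm, 0.05/6 (formula) | One arm, 0.05/6 (simulated) | Two-arm interaction | Two-arm joint test |
|---|---|---|---|---|---|---|
| 0.2 | 35% | 36% | 15% | 14% | 5.4% | 3.0% |
| 0.3 | 68% | 69% | 41% | 42% | 5.4% | 4.6% |
| 0.4 | 91% | 93% | 75% | 77% | 4.9% | 4.8% |
| 0.5 | 99% | 99% | 95% | 95% | 4.7% | 5.1% |

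Giving BWL a 0.5 SD effect on fatigue, still with none on the candidate, barely changes the one-arm rates (for example 68% instead of 69% at r = 0.3). In this setting, the one-arm result carries almost no information on whether the light worked.

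**4. What the two-arm analysis can detect.** For an interaction with 64 per arm and residual SD 1, the difference in standardized slopes detectable with 80% power is (1.960 + 0.842) × √(2/64) = 0.495, about 0.50.

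**The case against.** The strongest defence is that the one-arm model does not stand alone. The randomized comparisons of fatigue and of each continuous secondary outcome appear in the same plan, so a null effect of BWL on fatigue or on a candidate would be visible. This stands: the path from arm to candidate is covered. What remains uncovered is the link to the effect on fatigue, and that is what the third secondary objective asks about.

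The analysis is also labelled exploratory, belongs to a secondary objective and has adjusted p-values. That limits its importance but does not repair it. Adjustment guards against chance findings, whereas the within-arm association is real and answers a different question.

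The article speaks of prediction, not causation. A reader might infer that every significant slope would be published as a mechanism. The documents do not say so.

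Three other stronger readings are not supported:

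- **That the model shrinks to 25 patients at two visits.** Melatonin is collected in a subgroup of 25 per condition (Salivary melatonin), but the article specifies neither one joint model nor complete-case deletion. Cortisol is collected from all participants, and actigraphy is worn at all four measurement points.
- **That activity rhythms are missing from the variable list.** The Abstract counts activity among the biological circadian rhythms, although the objective names it separately. Only the inflammation markers are clearly absent.
- **That a two-arm mediation test would be simply correct.** Its path from mediator to fatigue is not randomized.

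**Conclusion.** The point holds. The plan assigns a one-arm regression to an objective about between-arm effects, and no other stated analysis fills the gap. Under assumed correlations of 0.2 to 0.5, equal in both arms, the one-arm test flags a variable that BWL does not change in about 35% to 99% of trials unadjusted, and in about 14% to 95% after Bonferroni over six variables. The two-arm tests give about 5% or less. The size depends on correlations that the documents do not give and on a single-variable simplification. The logical gap depends on neither. Separately, the objective names inflammation markers and the model's list does not. The damage is confined to the third secondary objective; the primary comparison and the sample size are untouched.

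**What to change.** Fit this analysis in both randomized arms.

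1. **Third secondary objective.** Use an exploratory mediation model for each mediator separately: arm to T0–T1 change in the mediator, and that change to later fatigue (for example at T2, which keeps the time order), adjusted for arm and baseline values. State that the path from mediator to fatigue is not randomized and rests on the assumption of no unmeasured confounding.
2. **Predictors of efficacy.** Use arm-by-baseline-variable interactions on fatigue.
3. **Variable list.** Add the inflammation markers that the objective names.
4. **Minimum alternative.** Keep the one-arm model, but describe it as correlates of fatigue within the BWL arm and draw no conclusion from it about efficacy or mechanism.

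The cost is revised analysis wording and some extra modelling. The comparison arm already supplies the measurements. Power is modest: an interaction reaches 80% only for a standardized slope difference near 0.50, so these results must stay exploratory.
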